### Recruitment {15}

To achieve adequate participant enrollment, we contacted beforehand eligible study centers with a minimum of 10 tonsil surgeries per year beforehand. Based on the letters of intent of the first 20 responses, the target numbers for 20 study centers reached already 947 cases for a recruitment period of 24 months. Therefore, we plan 20 study centers for TOTO. For the unlikely event of insufficient recruitment, we have about 10 other study centers on a waiting list.

## Assignment of interventions: allocation

### Sequence generation {16a}, concealment mechanism {16b}, and implementation {16c}

Block randomization with random block lengths will be used to allocate participants to the two groups of tonsil surgery in a 1:1 ratio, stratified by center and age (< 18 years, ≥ 18 years). Randomization will be administered centrally via the TOTO organization team using a web-based system, accessible by the principal investigator or delegated individual of each study center. The randomization list will be computer generated and provided by the trial statistician. On-site study personnel will perform the randomization.

## Assignment of interventions: blinding

### Who will be blinded {17a}

Participants and involved otolaryngologists will not be blinded. Blinding is not possible because it will be obvious for the participant/parents and involved otolaryngologists when looking into the mouth, if a tonsillotomy or a tonsillectomy was performed. Furthermore, postoperative pain is normally much lower after tonsillotomy. The involved biostatistician will be blinded until database lock. The assessment of the primary endpoint and secondary endpoints is following a strict evaluation algorithm. The blinded statistician and an independent otolaryngologist make up the endpoint committee. If an individual evaluation of an endpoint remains unclear, the endpoint committee will discuss the case. All confirmatory analyses will be comprehensively specified in the predefined statistical analysis plan to avoid any reporting bias.

### Procedure for unblinding if needed {17b}

Not applicable as no unblinding is part of this trial.

### Plans to promote participant retention and complete follow-up {18b}

The primary objective of the trial is to collect long-term data up to 24 months after tonsil surgery. The measurement of the days with sore throat and also the PROM results are depending on the information given by the participants. Therefore, a follow-up visit to the study center is not necessary. Furthermore, it can be presumed that the motivation of participants without any further complaints will decrease the longer the study takes. For these reasons, we decided to use a mobile application, i.e., the TOTO app, to collect the sore throat data during the follow-up. Using a push function, it is easy to prompt the participants and to remember the participants to answer the weekly questions. If the participant has no sore throat, the weekly push call via the app is answered with one click. The survey is only opened if the participant had a sore throat in the previous 7 days. Furthermore, the study center will call participants, if they have not answered through the app repeatedly. The diaries will be collected every 6 months.

### Data management {19}

For the pseudonymized collection of pseudonymized patient data, the coordinating center configures and provides an electronic case report form (eCRF) in good clinical practice (GCP)-compliant browser-based electronic data capture (EDC; SecuTrial®, Berlin, Germany). In particular, user rights can be managed via the EDC, data can be signed, any changes can be tracked via a prescribed audit trial, and the query management can be mapped. Data are entered at appropriate intervals after the source data has been created. Data are entered exclusively by authorized personnel at the study centers or, in the case of the PROMs, by the participants themselves using the TOTO app. The data are viewed on the principle of economy, i.e., each authorized user in the database can only view the data that is necessary for the fulfillment of his role. After completing the data entry and cleaning up the database, the data are handed over to the responsible biometrician for evaluation and a copy of the data for archiving to the sponsor.

The following source data are transferred from the center to the eCRF: inclusion criteria, exclusion criteria, demographic data (age, gender, employment relationship/child care relationship), additional adenoidectomy, TAHSI, TOI-14, SF-12, app usage, diary usage, documentation of adverse events (AEs). Each study center will be authorized to open a participant access to the database. The log-in takes place via the pseudonym assigned by the study center to ensure the anonymity of the participant data. The database access enables participants to make entries in the database either via the TOTO app or via a web-browser on the internet. The participants regularly provide the following data: day of sore throat (weekly basis), and in case of a sore throat, data on sore throat-related limitations, and drug use. The participant data are regularly checked for completeness. If the patient-reported outcomes are repeatedly not entered, this is automatically reported to the study center, which contacts the participant by phone to offer assistance. In addition, the reason for a possible non-entry is surveyed every 6 months for the telephone interview. If a paper-based diary is provided for participants who did not want to participate in electronic data collection, this diary is transferred from the study centers to the database every 6 months.

Several quality assurance measures will take effect at various levels to meet the quality of the data collected but also the requirements of the ICH GCP (as a reference system). At the implementation level, quality assurance will be carried out in accordance with the existing SOPs of the study center in Göttingen, Germany. This includes, among other things, that pre-study visits and initiation visits take place before the centers open and that the monitoring would be implemented according to a study-specific monitoring plan. As part of a risk-based management approach, risk-adapted monitoring and project management strategies will come into play. The data will be collected via a separate eCRF system (SecuTrial). This system uses a specific role concept with different authorizations for centers, monitors, and data managers. All data entries including deletions and changes can be tracked via an audit trail. Automatic checks for plausibility and correctness of the data will be implemented. Query management for questionable data entries is performed. The database is validated before commissioning. The database is not closed until the database is cleaned up.

### Confidentiality {27}

Personal data will be regarded as strictly confidential. A unique participant ID will be assigned to each participant at randomization. Participants/parents have to give consent for their contact details (name, address, phone numbers, and email address) to be used for the telephone interviews during follow-up. All electronic personal information will be kept on password-protected databases with restricted access and paper forms securely filed in a locked cabinet. Only the clinical team at the participating study center will have access to key data, which links study identifiers to individual datasets. All data transfer from the study centers and transferred from the participants directly via the app will be pseudonymized. These data are saved on local servers (RAID 10 system with daily backups) at the TOTO coordinating center Saved backups are available for up to 20 days. All processes comply with the requirements of the German general data protection regulations. All study records and Investigator Site Files will be kept GCP-conform at a site in a locked filing cabinet with restricted access.

Furthermore, a study-specific data protection concept will be developed. The patient-identifying information is only kept at the patient-treating center (the study center) and is stored with restricted access. Inspections are only carried out by specially authorized personnel (e.g., monitors) to whom reference was made in the declaration of consent. The anonymized data set will finally be published together with the primary results to ensure transparency.

### Plans for collection, laboratory evaluation, and storage of biological specimens for genetic or molecular analysis in this trial/future use {33}

Not applicable as no genetic or molecular analyses are part of this trial.

## Statistical methods

### Statistical methods for primary and secondary outcomes {20a}

Continuous variables will be presented as means and standard deviation or median and interquartile range (IQR) if not normally distributed. Categorical data will be presented as a number with a percentage. The primary analysis is performed on the per-protocol (PP) set and sensitivity analyses in the intention-to-treat (ITT) and full analysis population are also planned.

Differences between the observed risks of events (for primary outcomes of sore throat days) between both groups will be calculated along with their 95% confidence intervals by negative binomial regression. The non-inferiority of the tonsillotomy compared to the tonsillectomy in the number of symptomatic sore throat days within 24 months is evaluated by means of negative binomial regression with the stratification factors as a covariate and the non-inferiority margin of 0.8 to a one-sided significance level of 2.5%. In secondary outcome, the number of symptomatic sore throat days within 12 months after surgery is evaluated using the negative binomial regression with the stratification factors as a covariate and the non-inferiority margin of 0.8. Other parameters like the PROM results are evaluated using analyses of covariance (ANCOVA), with the stratification variables and baseline observations as covariates. Number of days with the inability to work/attend kindergarten/school after 24 months are evaluated by negative binomial regression with stratification variables as covariates. A one-sided significance level of 2.5% will be considered statistically significant (or 5% when testing two-sided). All confirmatory analyses are fully specified in a statistical analysis plan (SAP), which is written before database lock and before unblinding the trial statistician, in order to avoid reporting bias. The results are published independently of the statistical results in order to avoid publication bias.

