### Eligibility criteria {10}

#### Inclusion criteria

Age ≥ 3 years≥ 6 episodes of physician-diagnosed tonsillitis treated with antibiotics within the last 12 months or 3–5 episodes, if (a) further episodes occur in the next 6 months and a total number of 6 episodes is reached, or (b) there are additional patient-specific factors (special personal or professional concern, severe symptoms during the tonsillitis episodes, individual patient request) according to the German guideline for the treatment of tonsillitis [4].Subject (or parents/caregivers in case of underage participants) has provided written informed consent for participation in the study prior to any study-specific procedures

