### Sample size {14}

Non-inferiority of a tonsillotomy compared to tonsillectomy is given when the threshold of the lower limit of the 95% confidence interval for a difference in the number of days of sore throat is above 80%. Assuming a rate of 7.56 days within 24 months in both groups, a dispersion parameter of 0.44, and a significance level of 2.5%, a negative binomial regression analysis would detect a significant difference of the quotient of the rates compared to a non-inferiority limit of 0.8 with an 80% power, if 181 participants were treated in both arms. Assuming a loss of follow-up data of 20%, 454 patients have to be randomized.

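### The primary sore throat model adjusts only for centre and age group; one prespecified baseline score could add precision at no data cost

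*Protocol article*

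**What the plan says.** Statistical methods {20a} of the protocol article specifies the primary test as "negative binomial regression with the stratification factors as a covariate and the non-inferiority margin of 0.8 to a one-sided significance level of 2.5" per cent. Sequence generation {16a} names the factors: randomisation is "stratified by center and age (< 18 years, ≥ 18 years". The confirmatory model as stated therefore contains treatment, centre and age group.

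Baseline burden varies by design. The inclusion criteria admit patients with six or more treated episodes in 12 months. They also admit patients with 3–5 episodes who go on to reach six, or for whom "there are additional patient-specific factors (special personal or professional concern, severe symptoms during the tonsillitis episodes, individual patient request" applies.

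Disease-specific scores exist before surgery. Table 1 and Plans for assessment {18a} schedule the TAHSI, TOI-14 and SF-12 preoperatively. Data management {19} lists all three among the eCRF items, in a sentence that begins "The following source data are transferred from the center to the eCRF: inclusion criteria, exclusion criteria, demographic data". That list has no separate count of prior episodes.

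For the questionnaire outcomes, {20a} plans ANCOVA "with the stratification variables and baseline observations as covariates". It also says that the confirmatory analyses are fully specified in an SAP, which is not at hand.

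**The concern.** In a negative binomial model, part of the variance of the log rate ratio is Poisson noise and part is dispersion between patients. A covariate that predicts a patient's sore throat rate reduces the second part. Under the plan's own assumptions that part dominates, so a predictive baseline score would narrow the confidence interval on which non-inferiority is judged.

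With a log link and randomised arms, the adjusted model still targets the same rate ratio. A precision gain would therefore not change the question being answered, and the data are already collected.

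**Working it through.** **Inputs from Sample size {14} and {20a}**
- Mean: "Assuming a rate of 7.56 days within 24 months in both groups", so the true ratio is 1.
- Dispersion k and level: "a dispersion parameter of 0.44, and a significance level of 2.5" per cent, one-sided according to {20a}.
- Margin 0.8, power 80%, 181 per arm, 20% loss, 454 randomised.

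Only |ln 0.8| = ln 1.25 = 0.2231 enters the formulas, so they do not depend on which way round the ratio is written.

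**Step 1: reproduce the plan's figure**

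n per arm = (z₀.₉₇₅ + z₀.₈₀)² × 2 × (1/μ + k) / (ln 0.8)²

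- 1/7.56 + 0.44 = 0.1323 + 0.44 = 0.5723
- (1.960 + 0.842)² = 7.849, and (ln 0.8)² = 0.04979
- n = 7.849 × 2 × 0.5723 / 0.04979 = 180.4, rounded up to 181
- 181 / 0.8 = 226.25, rounded up to 227 per arm, or 454 in total

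Both stated figures are reproduced with no prognostic covariate.

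**Step 2: share of variance that a covariate can act on**

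0.44 / 0.5723 = 77%.

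**Step 3: power if a score explains a share R of the dispersion**

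Replace k by 0.44 × (1 − R). Then SE = √(2 × (1/7.56 + k) / 181) and power = Φ(0.2231/SE − 1.960). The values of R are assumptions, because the article gives no prognostic strength.

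| R (assumed) | k | SE | Power at 181 per arm | n per arm for 80% | Total randomised |
|---|---|---|---|---|---|
| 0% | 0.440 | 0.0795 | 80.1% | 181 | 454 |
| 5% | 0.418 | 0.0780 | 81.6% | 174 | 436 |
| 10% | 0.396 | 0.0764 | 83.2% | 167 | 418 |
| 20% | 0.352 | 0.0732 | 86.2% | 153 | 384 |

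The last two columns only express the gain in patients. They are not a proposal to recruit fewer.

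**Step 4: simulation check**

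Settings: 1000 trials per row, 181 per arm, an assumed 50/50 binary covariate, total dispersion held at 0.44, and no stratification factors in either model.

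| Rate ratio of covariate (assumed) | Power, unadjusted | Power, adjusted |
|---|---|---|
| 1.0 | 81.1% | 81.3% |
| 1.25 | 81.0% | 82.5% |
| 1.5 | 79.9% | 83.1% |
| 2.0 | 82.0% | 89.7% |

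The Monte Carlo standard error of one entry is about √(0.8 × 0.2 / 1000) = 1.3 points. The two models in a row were fitted to the same simulated data. An uninformative covariate costs essentially nothing, and the gain grows with prognostic strength.

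**Step 5: what shrinks the gain**
- The article does not say whether 0.44 is a marginal or an adjusted dispersion. If it is already adjusted, the gain over the planned 80% is smaller.
- Outcomes {12} defines the primary outcome as episodes of at least three consecutive days, whereas 7.56 is in days. If every day fell in such an episode, the mean could be at most 7.56/3 = 2.52 episodes. Holding k at 0.44 (an assumption), the dispersion share falls to 0.44 / (1/2.52 + 0.44) = 0.44/0.8368 = 53% or less.

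**The case against.** Adjusting for the randomisation strata is a standard choice, and the planned 80% power is reached with it. Nothing here is miscalculated. That stands, and it rules out reading the point as an error in the sample size.

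A reader might infer that the plan gives away a known amount of power. The article does not support this. No section says that any preoperative measure predicts sore throat after the tonsils have been removed or reduced, so the gain may be close to zero.

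A reader might also infer an inconsistency, because the questionnaire analyses use baseline values and the primary analysis does not. That does not hold. The ANCOVA covariate is the preoperative value of the same instrument. The sore throat count has no baseline of its own, since weekly reporting starts after discharge.

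The candidate covariates have limits:
- The eCRF list names inclusion criteria but not the entry route or an episode count, so an episode category may not be available.
- That category is also not a clean scale of burden. Some patients with 3–5 episodes later reach six, and others qualify through severe symptoms.
- Plans for assessment {18a} says that the German TAHSI is validated only for adults and that the TOI-14 was developed for adults. The trial enrols from age 3, so either score may predict less well in children.

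Finally, the SAP may already add a covariate. But the article does not leave the covariates open: it names them. A change to that statement is therefore a change to something fixed, not a request to fill a gap.

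**Conclusion.** The point holds as a conditional, low-cost improvement. The stated primary model omits any baseline burden term although suitable scores are collected before surgery, and adding one prespecified score could improve precision without changing the estimand.

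For a score explaining 5% to 20% of the dispersion, the gain is about 1.5 to 6 percentage points of power at 181 per arm, and it is nil for a score that predicts nothing. This rests on three assumptions: the mean of 7.56 days, 0.44 as an unadjusted dispersion, and the assumed share explained. The stated design meets its power target without the change.

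**What to change.** In Statistical methods {20a}, and identically in the SAP before database lock and unblinding:

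1. Define the primary model as treatment, centre, age group and one named baseline score. The TOI-14 total is one candidate, with a note that it was developed for adults. Leaving a choice between TOI-14 and TAHSI would not prespecify the model.
2. State a simple imputation for a missing baseline score, applied without regard to arm.
3. Add the entry category (six or more versus 3–5 episodes) only if the eCRF records it.
4. Keep the model with strata only as a sensitivity analysis.
5. As a separate reporting item that does not bear on power, give the primary rate ratio descriptively by randomised age stratum (<18, ≥18 years). The subgroup analyses in Methods for additional analyses {20b} cover only days of absence.

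The cost is wording and a few lines of analysis code. No new data, visits or patients are needed.

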### Interim analyses {21b}

An interim analysis is not planned.

### Methods for additional analyses (e.g., subgroup analyses) {20b}

Subgroup analysis is planned for the subgroups of working participants and kindergarten/school visitors. The number of days with the inability to work or inability to attend kindergarten/school at the times 6 months, 12 months, 18 months, and 24 months are evaluated descriptively using the negative binomial regression in these subgroups

### Methods in analysis to handle protocol non-adherence and any statistical methods to handle missing data {20c}

The primary hypothesis of non-inferiority is carried out in the per protocol (PP) population. The criteria for serious protocol deviations that lead to exclusion from the analysis are recorded in SAP before the end of the data collection. The intention-to-treat population (ITT) contains all patients who were randomized to one of the treatments and also assigns them to the randomized treatment group. The non-inferiority is only tested in this population as a sensitivity analysis. Missing values are replaced with the help of multiple imputations. The imputation method is described in detail in SAP. The full analysis population consists of all participants who were randomized and operated on and who provided at least one indication of the occurrence of a sore throat. Missing values are also replaced with the help of multiple imputations. Finally, the safety analysis population consists of all patients who underwent surgery.

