### Criteria for discontinuing or modifying allocated interventions {11b}

If the assigned type of tonsil surgery is discontinued or modified, the patient has to be excluded from the per-protocol analysis.

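### Non-inferiority is decided on the per-protocol set alone in an open-label trial, with no requirement that the intention-to-treat analysis agree

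*Protocol article*

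**What the plan says.** Three sections of the protocol article fix the decision rule.

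- Statistical methods {20a} makes PP the primary set and gives ITT and the full analysis population the role of sensitivity analyses.
- Protocol non-adherence and missing data {20c}: "The primary hypothesis of non-inferiority is carried out in the per protocol (PP) population". Of the ITT population, which holds all randomized patients in their randomized arm with multiple imputation, it says: "The non-inferiority is only tested in this population as a sensitivity analysis".
- Section {11b}, on changes to the allocated operation, says: "If the assigned type of tonsil surgery is discontinued or modified, the patient has to be excluded from the per-protocol analysis".

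Further exclusion criteria are left to the analysis plan: "The criteria for serious protocol deviations that lead to exclusion from the analysis are recorded in SAP before the end of the data collection".

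On blinding, {17a} says: "Participants and involved otolaryngologists will not be blinded". The biostatistician is blinded until database lock.

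Two related statements bear on the analysis sets. Section {20c} defines the full analysis population as participants "who were randomized and operated on and who provided at least one indication of the occurrence of a sore throat". The sample size section {14} says: "Assuming a loss of follow-up data of 20%, 454 patients have to be randomized".

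**The concern.** Whether an operation was discontinued or modified is known only after randomization, and an unblinded surgeon decides it. Removing those patients breaks the comparison that randomization protects. If they differ in outcome from the rest of their arm, or are removed more often from one arm than the other, the PP ratio is no longer the randomized ratio.

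No sentence says what happens if PP meets the margin and ITT does not. As written, non-inferiority would be declared. The Discussion expects the result to inform the G-BA's decision on tonsillotomy, so a claim that depends on the choice of set would matter.

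Two smaller points follow. The full analysis wording, read literally, leaves out patients who never had a sore throat. The 20% allowance names lost follow-up data but not PP exclusions, although PP is the set on which the test is run.

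**Working it through.** **Inputs from the protocol.** Mean 7.56 sore throat days in 24 months in both arms, dispersion k = 0.44, margin 0.8, one-sided 2.5%, power 80%, 181 per arm, 20% loss, 454 randomized (all in {14}; the one-sided level is explicit in {20a}). More days are worse, so I read 0.8 as tonsillectomy over tonsillotomy, which is 1/0.8 = 1.25 for tonsillotomy over tonsillectomy.

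**Step 1: reproduce the sample size.** With a Wald test on the log rate ratio,

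n per arm = (1.960 + 0.842)² × 2 × (1/7.56 + 0.44) / (ln 0.8)² = 7.849 × 1.1446 / 0.04979 = 180.4, so 181.

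181/0.8 = 226.25, so 227 per arm and 454 in total. Both stated figures reproduce.

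**Step 2: the decision rule.** {20a} and {20c} agree that PP is the test and ITT a sensitivity analysis. {11b} fixes one PP exclusion. Nothing in these sections gives ITT a role in the conclusion.

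**Step 3: how much PP exclusions could matter.** The protocol gives neither a modification rate nor outcomes for such patients, so everything in this step is assumed. Let the true ratio in all patients be 1.25. Let a fraction f of the tonsillotomy arm be excluded, with h times the rate of the rest of that arm, and none of the tonsillectomy arm. Then

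- PP ratio r = 1.25 / (1 + f(h − 1))
- SE = √[(1/7.56 + 0.44)/181 + (1/(7.56r) + 0.44)/(181(1 − f))]
- one-sided type I error = Φ(ln(1.25/r)/SE − 1.960)

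| f | h | r | SE | Type I error |
|---|---|---|---|---|
| 2% | 1.5 | 1.25/1.01 = 1.238 | 0.0790 | Φ(0.126 − 1.960) = 3.3% |
| 5% | 2 | 1.25/1.05 = 1.190 | 0.0798 | Φ(0.611 − 1.960) = 8.9% |
| 5% | 0.5 | 1.25/0.975 = 1.282 | 0.0795 | Φ(−0.318 − 1.960) = 1.1% |

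The last row shows the opposite case: if the excluded patients do better than the rest, PP becomes conservative.

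**Step 4: full analysis population, literal reading.** For a negative binomial count, P(0) = (1 + kμ)^(−1/k).

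- Tonsillectomy, μ = 7.56: 4.326^(−2.273) = 3.6%
- Tonsillotomy at the margin, μ = 9.45: 5.158^(−2.273) = 2.4%
- Means among those with at least one day: 7.56/0.9642 = 7.84 and 9.45/0.9760 = 9.68
- Ratio: 1.235 instead of 1.25

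**Step 5: the 20% allowance.** 227 × 0.8 = 181.6 per arm remain after lost follow-up. Power = Φ(0.2231/√(2 × 0.5723/n) − 1.960).

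- No further exclusion, n = 181.6: 80.3%
- A further 5% (assumed), n = 172.5: 78.2%
- A further 10% (assumed), n = 163.4: 76.0%

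**The case against.** PP is a usual primary set for non-inferiority, because keeping crossovers in their randomized arm can dilute a real difference. If a tonsillotomy were extended to a full tonsillectomy, ITT would make the arms more alike and excluding that patient would be the cautious choice. The {11b} rule applies to both arms, an ITT analysis with multiple imputation is planned, and results are to be published whatever they show. All of this stands. It shows that either set can mislead, which is a reason for requiring both and not for relying on PP alone.

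Four stronger readings are tempting, but the document does not support them.

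- *PP is biased towards tonsillotomy.* Section {11c} treats the extent of tonsillotomy as the part that needs control, which makes unequal exclusions plausible. Neither their frequency nor their direction is given.
- *The full analysis population selects on outcome and so favours the claim.* The weekly question described in {13} and {18a} is yes or no, and a no can also count as an indication about occurrence. The set carries no claim. Even literally read, the shift on days is only to 1.235. A larger shift, to about 1.19, appears only for episodes with a mean of 7.56/3 = 2.52 and the days dispersion. Neither of these is given for episodes.
- *Exclusion criteria can be tuned late.* Leaving them to the SAP is ordinary. The SAP precedes both database lock and the statistician's unblinding.
- *The 20% allowance helps the claim.* Lost power makes non-inferiority harder to show.

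**Conclusion.** The point holds for the decision rule. In an open-label surgical trial, non-inferiority rests on one set formed after randomization, and it can be declared even if ITT does not support it. Choosing PP is not itself an error; letting it stand alone is the weakness.

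The size cannot be derived from the protocol. Under the assumed one-arm exclusions that work against the control of error, the one-sided type I error rises from 2.5% to about 3.3% (2% excluded, 1.5 times the rate) or about 9% (5% excluded, twice the rate). With the opposite assumption it falls below 2.5%.

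The full analysis wording is a matter of clarity in a sensitivity set, with a small effect on days. The 20% allowance is minor: about 78% or 76% power if a further 5% or 10% were excluded.

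**What to change.** 1. State that non-inferiority is claimed only if the confidence limit meets the stated margin (0.8, equivalent to 1.25 for tonsillotomy over tonsillectomy) in both the PP and the ITT analyses. The cost is a small loss of power, small because the two sets overlap heavily. The sample size formula and its inputs do not change, so 181 per arm and 454 randomized can stay.
2. Define the full analysis population as randomized, operated on, and with at least one completed weekly report, whether the answer on sore throat is yes or no. This is a wording change only.
3. State that the 20% allowance includes PP exclusions, or restate the power expected in the PP set. This is also wording, unless the expected exclusions turn out large enough to call for more patients.
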